## **6.2 Missing data**

Since the POAF occurrence will be obtained from monitoring devices in participant's hospitalization, missing data won't be expected.

## **7. Subgroup analysis for the primary outcome**

Subgroup analysis will be conducted based on the risk factors of POAF reported by previous studies as follows: sex, age ( $\geq 65$  years vs.  $< 65$  years), LVEF ( $> 55\%$  vs.  $\leq 55\%$ ), body mass index ( $\geq 25$  kg/m^2 vs.  $< 25$  kg/m^2), left atrium size ( $\geq 40$  mm vs.  $< 40$  mm), and history of myocardial infarction, diabetes mellitus and hypertension.

To test for a differential effect of randomized treatment across subgroups, an interaction term (treatment group by subgroup) will be fitted in the Cox proportional hazards model. If proportional hazards cannot be assumed a multiple logistic regression model will be fitted.

Subgroup analyses will be conducted only with respect to the primary outcome.

Treatment effect in each subgroup shall be presented along with the P value for the interaction term in the model.

All patients randomized shall be included in the analysis, irrespective of whether surgery was undertaken.

## **8. Statistical test for secondary endpoints**

### **8.1 Statistical analysis method**

Secondary outcomes including safety and economics will also be analyzed according to approach mentioned in 4.2. Unless otherwise stated, statistical significance level is set to 0.05 (2-sided).

For clinical concerns, the incidence of epicardial effusion within 30 days after discharge and arrhythmias other than AF within 30 days after discharge will be analysed as delayed epicardial effusion and critical arrhythmias, respectively. Delayed epicardial effusion was defined as new-onset epicardial effusion (moderate or more) within 30 days after discharge. Critical arrhythmias other than AF was defined as arrhythmias requiring immediate clinical intervention, such as complete atrioventricular block.

Since POAF happens after surgery and has a effect on postoperative clinical events, we think the analysis of all cost during hospitalization may not be appropriate. Only postoperative cost for each patient will be included in the final analysis. Similarly, only postoperative length of hospitalization will be included in the final analysis.

Although the follow-up visit of 30 days is relative short, we intend to compare the MACCE outcome between the 2 groups in the final manuscript.

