## **1.3 Rationale of conducting this trial**

As mentioned before, there is lack of specific recommendation of approach for preventing POAF after CABG except of beta-blockers and the related surgical means of ANMTs are still underestimated. Therefore, here in this study, we will focus on reevaluating the effect of partial cardiac denervation on preventing POAF after CABG in a larger population through more complete and longer duration of continuous ECG monitoring. To begin with, previous studies showed that the ligament of Marshall (LOM) is the critical site of CANS participating in the occurrence of atrial fibrillation (AF). Kim et al. noticed that the LOM contained sympathetic nerve fibers, and had insertions into the myocardium of the left atrium and coronary sinus, providing the essentials for the formation of arrhythmia. Other reports clearly implicated the LOM and adjacent atrium as the origins of arrhythmias. In addition, Haemers et al. showed that right atrium was obviously infiltrated by adipose tissue in patients with AF, especially in those with persistent AF. Besides, cutting off the LOM and resecting the fat pad along the Waterston groove is routinely used in maze surgery to treat patients with AF. Lastly, this trial also aims to seek for a safe, simple and convenient way to prevent POAF after CABG. We believe that choosing one site at both right and left

atrium namely the LOM and the fat pad along the Waterston groove, exactly meets our purpose.

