### **3.5 Sample size justification**

Two parallel arms will be required. The occurrence of POAF after cardiac surgery was about 23%, according to the prior study. Based on a detailed reviewing of the existing

studies, cardiac denervation reduces the incidence of POAF by 50%. Therefore, with 80% power and 0.05 alpha, 408 participants are needed to detect 23% POAF rate in the control group and a reduction by 50% in the intervention group. Taking into account a 5% protocol violation rate and patient loss/dropout, a population size of 430 (215 in each group) shall be sufficient for this investigation. As one of the world's largest centers of cardiovascular diseases, Fuwai Hospital completes more than 10 thousand cardiac surgeries every year, of which an approximate of 5 thousand are isolated CABG. This trial shall be completed in due course.

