### **4.2 Baseline comparability of randomized groups**

Demographic and clinical characteristics of patients at baseline will be presented by randomised group. Number of subjects, mean, standard deviation, median, interquartile range (IQR), minimum, and maximum will be used for description of continuous variables. Continuous variables will be tested by Student's t test if normally distributed; otherwise, by the Mann-Whitney U test. Counts and percentages will be used to summarize the categorical variables. Chi-squared test or Fisher's exact test will be applied for categorical variables, as appropriate.

Intraoperative data such as number of grafts, % off pump, % saphenous vein/radial artery, duration of operation will also be presented.

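### Binary safety outcomes and MACCE are compared by p-values alone; for a rare harm, a non-significant result at 215 per arm says little about safety

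*Supplement*

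**What the plan says.** The SAP lists eight secondary outcomes in section 2.2, five of them under the safety heading. SAP v3.0 section 8.1 adds a MACCE comparison and narrows two of the five: effusion to new-onset effusion of at least moderate size, and arrhythmia to events needing immediate intervention. For all of them the method is one sentence: "Secondary outcomes including safety and economics will also be analyzed according to approach mentioned in 4.2". The significance level is two-sided 0.05.

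For binary data section 4.2 says "Counts and percentages will be used to summarize the categorical variables" and "Chi-squared test or Fisher's exact test will be applied for categorical variables, as appropriate". It gives no measure of effect and no interval. Section 8.1 of protocol v2.0 adds neither. The SAP asks for a treatment effect only in section 7, for subgroups of the primary outcome.

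The sample size (SAP section 3.5) rests on POAF alone: "408 participants are needed to detect 23% POAF rate in the control group and a reduction by 50% in the intervention group", raised to 430 (215 per arm) for 5% violation or loss. No expected rate is given for any safety outcome. The rationale (SAP section 1.3) says that "this trial also aims to seek for a safe, simple and convenient way to prevent POAF after CABG".

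**The concern.** Denervation is an extra surgical step added to prevent a complication. Whether it is worth adopting depends partly on how much excess harm the trial can rule out. A p-value does not answer that question. With few events it will tend to be non-significant whether or not the procedure causes harm, and the planned output contains nothing that shows how large an excess remains possible. At stake is what the trial can say about harm. The primary POAF result is not affected.

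**Working it through.** **1. The plan's own figure.** Inputs from SAP section 3.5: control rate 23%, halved, 80% power, alpha 0.05. With p1 = 0.23, p2 = 0.12 (the halved rate rounded up) and mean 0.175:

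m = [1.96·√(2·0.175·0.825) + 0.842·√(0.23·0.77 + 0.12·0.88)]² / 0.11² = 186.1 per arm.

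With the continuity correction, n = (m/4)·[1 + √(1 + 4/(0.11·m))]² = 203.9, so 204 per arm and 408 in total. Then 408/0.95 = 429.5, so 430. The plan does not name its formula. Unrounded 11.5% gives 338 without and 372 with the correction; it also gives 408 if alpha is set to 0.025 two-sided without the correction. On every route, the only rates that enter are POAF rates.

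**2. Power for a doubled harm at 215 per arm.** The control rates are assumptions, because the documents give none. The normal approximation is

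power ≈ Φ[(Δ − 1.96·s0)/s1], with s0 = √(2·p̄(1−p̄)/215) and s1 = √{[p1(1−p1) + p2(1−p2)]/215}.

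For 2% vs 4%: s0 = 0.01645, s1 = 0.01642, (0.02 − 0.03225)/0.01642 = −0.746, and power = 23%.

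The exact figures sum the probabilities of all pairs of binomial counts for which the test gives p < 0.05 (chi-squared without continuity correction):

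| Control vs denervation | Approx. power | Chi-squared: power / missed | Fisher: power / missed |
|---|---|---|---|
| 1% vs 2% | 13% | 12% / 88% | 5% / 95% |
| 2% vs 4% | 23% | 23% / 77% | 14% / 86% |
| 3% vs 6% | 32% | 32% / 68% | 25% / 75% |
| 5% vs 10% | 50% | 50% / 50% | 44% / 56% |
| 10% vs 20% | 83% | 84% / 16% | 80% / 20% |

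By the approximation, power for a doubling passes 50% at a control rate of about 5.0% and 80% at about 9.4%. With 204 per arm after losses, power is up to about 3 points lower.

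**3. What an interval would add.** Take 4 control and 10 denervation events out of 215 each. Fisher p = 0.17. The risk difference is 4.65 − 1.86 = 2.79 points. The Wilson limits are 0.73% to 4.69% (control) and 2.55% to 8.35% (denervation). Newcombe limits:

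- lower: 2.79 − √[(4.65 − 2.55)² + (4.69 − 1.86)²] = −0.7 points
- upper: 2.79 + √[(8.35 − 4.65)² + (1.86 − 0.73)²] = +6.7 points

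So an excess of more than 6 per 100 is not excluded. Equal counts, 4 vs 4, give p = 1.0 but still leave an excess of up to 3.0 points open.

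**4. Two outcomes with a special structure.**

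- Re-operation is counted only when the bleeding was caused by the denervation (SAP section 2.2.1). As worded, no control patient can have the event, so a doubling is undefined. Against a fixed zero, 5 events give Fisher p = 0.061 and 6 give p = 0.030.
- Conversion to on-pump surgery can occur only in patients who start off-pump. If that is half of them (assumption, about 108 per arm), power for 5% vs 10% falls to 29%.

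**The case against.** The strongest points on the other side are these:

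- Sizing a trial on its primary outcome is ordinary practice, and secondary outcomes were never promised 80% power. This stands, and the point is not that the sample is too small.
- No safety rate appears in the documents, so rarity is assumed. This stands. The narrowed definitions of effusion and arrhythmia can only lower those two rates, but how low they are is unknown.
- Arm-level counts and percentages will be reported, so a reader can compute an interval. True, but the plan should itself state the quantity on which its harm conclusion rests.
- Harms are analysed both by intention to treat and per protocol, adverse events are recorded individually, and serious events go to the review board and to a monitoring committee whose stopping criterion adds a causal judgement. These are real safeguards. None of them estimates the excess harm with its uncertainty.

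Two stronger readings are tempting. One is that the plan will treat a non-significant result as proof of safety. No section says so: the research hypothesis concerns efficacy only, and the remark about a safe procedure introduces the choice of the two anatomical sites. The other is that every safety outcome is underpowered. That fails for common outcomes. If transfusion is needed in 10% or more of control patients (assumption), a doubling would be detected with about 80% power or more.

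**Conclusion.** The point holds in a limited form. What rests on the text alone is that the binary safety outcomes and MACCE are compared between arms only by chi-squared or Fisher p-values at two-sided 0.05, with no effect estimate or interval, in a sample sized on POAF. What rests on an assumption is the size of the consequence: for harms with a control rate below about 5%, a doubling would be missed at least about half the time, rising to 88% (chi-squared) or 95% (Fisher) at 1% vs 2%. For those outcomes a non-significant result is uninformative about safety. The power argument does not extend to common outcomes, though the missing estimate and interval apply to them as well.

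**What to change.** In SAP section 8.1, replace the reference to section 4.2 for the binary safety outcomes and MACCE with the following:

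- The main safety analysis is the between-arm risk difference (denervation minus control) with a two-sided 95% confidence interval, Newcombe or Miettinen-Nurminen, with one method named in advance. Where safety is analysed in both the intention-to-treat and per-protocol sets, give it in both.
- Harm is interpreted from the upper limit, that is, the largest excess not ruled out.
- A non-significant p-value is not evidence of safety or of no difference. P-values stay as supplementary. With few events a Fisher p-value and the interval can disagree about zero, so say that the interval governs.
- For re-operation, compare all re-operations for bleeding in both arms, because the attributed version has no control counterpart.

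The cost is a few sentences of SAP text and a few lines of code, with no extra patients or data. The downside is a more guarded safety statement. The change sets no margin for acceptable harm, so it shows what excess has been ruled out and leaves to clinical judgement whether that is small enough.

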| Post-operative atrial fibrillation    |                         |                |                 | X                                   | X                             |
| Time spent in atrial fibrillation     |                         |                |                 | X                                   |                               |
| Blood transfusion                     |                         |                | X               | X                                   |                               |
| Transferring to on-pump CABG          |                         |                | X               |                                     |                               |
| Re-operation                          |                         |                |                 | X                                   |                               |
| Delayed pericardial effusion          |                         |                |                 |                                     | X                             |
| Arrhythmias exclude of AF             |                         |                |                 | X                                   | X                             |
| Postoperative length of hospital stay |                         |                |                 | X                                   |                               |
| All costs after surgery               |                         |                |                 | X                                   |                               |
| MACCE during the 30-day follow-up     |                         |                |                 |                                     | X                             |

**Figure 1. Standard Protocol Items: Recommendations for Interventional Trials (SPIRIT).** AF, atrial fibrillation.

During the primary screening, patients will be evaluated for the eligibility into the study, and an individual informed consent will be signed at the willingness of each patient. Then, participants will be randomly allocated to either intervention or control

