### **6.3 Data collection at postoperative hospitalization**

Since POAF is influenced by a great deal of aspects, data collection shall be comprehensive. Both intraoperative characteristics and postoperative data will be collected at this period:

- 1) Operation time, cardiopulmonary time, cross clamp time, number of total/artery/venous grafts.
- 2) Postoperative laboratory tests and examinations: blood, biochemistry, coagulation, biomarker, transthoracic echocardiography and 12-lead-ECG at discharge.
- 3) Intensive care unit stay, length of hospitalization, postoperative costs, blood transfusion, secondary operation, complications such as stroke, acute kidney injury and postoperative myocardial infarction.

- 4) The prescription of medications in postoperative hospitalization and at discharge.
- 5) The continuous ECG monitoring device will be removed from participants at discharge and handed to function test department for data exportation and analysis.

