## **6.4 Data collection at follow-up visit**

The 30-day follow-up after discharge will be completed by outpatient visit and/or phone calls. During this period, following data will be collected:

- 1) MACCE: the composite of all-cause death, myocardial infarction, stroke and repeat coronary revascularization during these 30 days.
- 2) Transthoracic echocardiography and 12-lead-ECG at the 30 day after discharge.
- 3) Any arrhythmias experience confirmed by ECG and related treatment.

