## **1.4 Benefit /risk and ethical assessment**

The intervention group will receive additional partial cardiac denervation procedure, namely cutting off the LOM and resecting the fat pad along the Waterston groove. Potential risks are as follows: extending operation time, increasing intraoperative blood loss and postoperative arrhythmias. The related technique has been applied in surgical treatment of AF and proved to be safe and feasible. The surgery will remove only part of the CANS and will not affect the patient's normal sinus rhythm. All the participants can contact the the study physician who will help them to get the right medical treatment, if any suspected arrhythmias-related adverse events emerge after surgery. The study will be approved by the Institutional Review Board of Fuwai Hospital.

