## **2.2 Secondary objectives**

### **2.2.1 Safety assessments**

- 1) The incidence of transferring to on-pump CABG intraoperatively;
- 2) The need for blood transfusion;
- 3) Re-operation for postoperative bleeding caused by partial cardiac denervation procedure;
- 4) The incidence of epicardial effusion within 30 days after discharge;
- 5) Arrhythmias other than AF within 30 days after discharge;

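### MACCE and effusion are counted only from discharge, so in-hospital death, stroke, MI, repeat revascularisation and early effusion enter no named between-arm endpoint; the non-AF arrhythmia window is contradictory

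*Supplement*

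**What the plan says.** **Effusion.** The latest SAP (8.1, secondary endpoints) states: "Delayed epicardial effusion was defined as new-onset epicardial effusion (moderate or more) within 30 days after discharge". Protocol Figure 1 (section 3.1) lists delayed pericardial effusion and marks it at the follow-up visit only.

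**MACCE.** Protocol 6.4 opens with the 30-day follow-up after discharge and then defines the outcome: "MACCE: the composite of all-cause death, myocardial infarction, stroke and repeat coronary revascularization during these 30 days". Figure 1 has the row "MACCE during the 30-day follow-up", marked at the follow-up visit only. SAP 8.1 adds a comparison between the two groups but gives no earlier start.

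**Non-AF arrhythmia.** The objective in protocol and SAP 2.2.1 is "Arrhythmias other than AF within 30 days after discharge". SAP 8.1 says that "arrhythmias other than AF within 30 days after discharge will be analysed as delayed epicardial effusion and critical arrhythmias, respectively", and then adds a severity criterion: "Critical arrhythmias other than AF was defined as arrhythmias requiring immediate clinical intervention, such as complete atrioventricular block". Figure 1, however, marks non-AF arrhythmia in the postoperative hospital stay as well as at follow-up.

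**In-hospital data.** Protocol 6.3 collects "complications such as stroke, acute kidney injury and postoperative myocardial infarction". Protocol 3.1 and SAP 3.3 have pericardial effusion assessed after surgery, with an echocardiogram on the day of discharge. Protocol 7.3 records all AEs and SAEs, including dates of death.

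**Other safety comparisons.** Section 2.2.1 also lists conversion to on-pump surgery, transfusion, and re-operation for bleeding caused by the denervation. Protocol section 9 has a stopping rule that refers to a between-group difference in mortality or SAEs.

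**The concern.** The exposure takes place in the operating room, and the plan itself expects its risks to arise then or soon afterwards: "Potential risks are as follows: extending operation time, increasing intraoperative blood loss and postoperative arrhythmias". A window that opens at discharge leaves out the first postoperative days. A stroke, infarction or death on the ward is no MACCE event under the protocol's definition, and an effusion found before discharge is not new-onset after discharge.

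Two further difficulties follow from the choice of start.

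- A patient who dies in hospital cannot have an event in a post-discharge window, so the most serious harm scores as nothing or as missing.
- Discharge happens after randomisation and may depend on treatment. The background sections say POAF lengthens hospital stay, and postoperative stay is itself a secondary outcome. If the procedure prevents POAF, the two arms may be observed over different stretches of postoperative time.

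Section 1.3 says the trial seeks a safe way to prevent POAF. The named endpoints could not support a safety statement on death, stroke, MI or early effusion. The same gap can hide benefit: the background says POAF raises stroke risk, but a stroke before discharge would not count.

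**Working it through.** The plan states no event rate or power for these outcomes, so there is no figure of its own to reproduce. The main check is a comparison of the passages.

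| Outcome | Recorded in hospital? | In a named between-arm endpoint before discharge? |
|---|---|---|
| Death | Through SAE recording (protocol 7.3) | No; MACCE starts at discharge (6.4) |
| Stroke, MI | Yes (6.3) | No; same reason |
| Repeat revascularisation | Not named; 6.3 lists secondary operation | No; same reason |
| Moderate or worse effusion | Effusion assessed (3.1; SAP 3.3) | No; must be new-onset after discharge (SAP 8.1) |
| Non-AF arrhythmia | Yes (Figure 1) | Unclear; label says after discharge, Figure 1 says both periods |
| Conversion, transfusion, re-operation for bleeding | Yes | Yes (2.2.1; SAP 8.1) |

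Of the five safety outcomes in 2.2.1, three are intraoperative or in-hospital and two carry the after-discharge label. MACCE, added in SAP 8.1, makes a third outcome tied to the follow-up.

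**Do the three in-hospital outcomes fill the gap?** No. Conversion can occur only in operations begun off-pump. Re-operation is limited to bleeding caused by the denervation, which cannot arise in a control patient who did not have it. None of the three measures death, stroke, MI or effusion.

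**Does another part of the SAP fill it?** SAP 5.2 defines the safety analysis sets but names no death, AE or SAE outcome. The stopping rule in protocol section 9 has no matching SAP analysis, and SAP section 10 plans no interim analysis.

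**Illustration of size.** The only input from the documents is 215 per arm. The rest is assumed: a control risk p of 2% or 5% from surgery to 30 days after discharge, a doubling with the procedure, and a share f of events before discharge that is equal in both arms.

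- Risks seen from discharge: control c = p(1 − f), procedure 2c. Expected events: 215c and 430c.
- Power (normal approximation, two-sided 0.05) = Φ{[c√215 − 1.96√(2m(1 − m))] / √[c(1 − c) + 2c(1 − 2c)]}, where m = 1.5c.
- Example, p = 2%, f = 0: c = 0.02, m = 0.03. The numerator is 0.293 − 0.473 = −0.180 and the denominator is 0.241, so Φ(−0.75) ≈ 0.23.

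| p | f | Expected events, control vs procedure | Power |
|---|---|---|---|
| 2% | 0 (from surgery) | 4.3 vs 8.6 | 23% |
| 2% | 50% | 2.1 vs 4.3 | 13% |
| 2% | 90% | 0.4 vs 0.9 | 6% |
| 5% | 0 (from surgery) | 10.8 vs 21.5 | 50% |
| 5% | 50% | 5.4 vs 10.8 | 28% |
| 5% | 90% | 1.1 vs 2.1 | 9% |

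The approximation is rough at such small counts; the table shows only the order of the loss. If the excess fell wholly before discharge, the post-discharge comparison would have no excess to find.

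**The case against.** The strongest reply is that the plan does look at the hospital period. Conversion, transfusion and re-operation are compared between arms. The primary endpoint covers supraventricular arrhythmia from surgery to day 6, and SAP 6.1 compares AF episodes, AF burden, heart rates and premature atrial contractions. All AEs and SAEs are recorded, and the DMC is told of SAEs. All of this stands. A reader might infer that no in-hospital harm is compared between the arms; the documents do not support that.

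A reader might also infer that in-hospital non-AF arrhythmia is missed entirely. That goes too far as well: Figure 1 schedules it in hospital, the critical-arrhythmia definition sets severity only, and the label could be read as giving an end date. What stands is a contradiction to be reconciled. The end-date reading is much harder to sustain for effusion and MACCE, given the words delayed and new-onset and the follow-up-only marks in Figure 1.

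Delayed effusion may be a deliberate outcome, which is a fair reason to keep it. It is no reason to leave early effusion out of every comparison.

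Finally, the documents do not say that in-hospital deaths leave the denominator. SAP 5.1 analyses all randomised patients except those without outcome information, and SAP 8.2 imputes nothing. How such a death would be scored is unstated.

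**Conclusion.** The point holds for MACCE and effusion: as written, in-hospital death, stroke, MI, repeat revascularisation and early effusion are in no named between-arm endpoint. For non-AF arrhythmia the supportable finding is that label and schedule disagree.

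The size cannot be taken from the documents. Under the assumed rates, the discharge window discards half to nine tenths of the events, and power falls from about 23–50% to about 6–28%. Power for a doubling is at most about one half even with the full window, so the trial could not settle these outcomes either way; the case for change is that the events be counted at all.

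A reader might infer a bias toward no difference. Loss of events and selection on survival to discharge are real concerns, but the direction of the selection is not shown, and each patient's window has the same nominal length of 30 days.

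This is a should-fix point. The outcomes are secondary or supplementary, and the primary endpoint, its test and the sample size are untouched.

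**What to change.** In SAP 8.1, protocol 2.2.1 and 6.4, and Figure 1:

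- Count MACCE (including in-hospital death, stroke, MI and repeat revascularisation), moderate-or-worse effusion and critical non-AF arrhythmia from surgery to a fixed postoperative day, or through the 30-day visit. A fixed day has the advantage that its end does not depend on discharge.
- Compare them by randomised arm with all randomised patients as denominator, and state how a patient who dies before the end of the window is scored for effusion and arrhythmia.
- Keep delayed (post-discharge) effusion and the split before and after discharge as descriptive results.
- Make the arrhythmia label agree with the schedule.
- Name a by-arm table of mortality and SAEs, so that the stopping rule in protocol section 9 has a matching analysis.

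The cost is mainly wording, some extra analysis, and outcomes that differ from the labels now in 2.2.1. In-hospital stroke, MI, effusion and arrhythmia are already collected or scheduled, and deaths come through SAE recording. The sponsor should check that the case report form identifies in-hospital repeat revascularisation and the grade and date of in-hospital effusion, which the protocol does not spell out.

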## **2.2 Secondary objectives**

### **2.2.1 Safety assessments**

- 1) The incidence of transferring to on-pump CABG intraoperatively;
- 2) The need for blood transfusion;
- 3) Re-operation for postoperative bleeding caused by partial cardiac denervation procedure;
- 4) The incidence of epicardial effusion within 30 days after discharge;
- 5) Arrhythmias other than AF within 30 days after discharge;

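### SAP 8.1 replaces two listed safety endpoints with severe-only versions and keeps no between-arm comparison of the endpoints as listed

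*Supplement*

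**What the plan says.** Protocol v2.0, section 2.2.1, and SAP v3.0, section 2.2.1, carry the same two items among five safety outcomes: "The incidence of epicardial effusion within 30 days after discharge" and "Arrhythmias other than AF within 30 days after discharge". Neither item has a grade, a new-onset condition or a treatment condition.

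SAP v3.0, section 8.1, says that these two endpoints "will be analysed as delayed epicardial effusion and critical arrhythmias, respectively". It then defines the replacements:

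- Effusion: "Delayed epicardial effusion was defined as new-onset epicardial effusion (moderate or more) within 30 days after discharge".
- Arrhythmia: "Critical arrhythmias other than AF was defined as arrhythmias requiring immediate clinical intervention, such as complete atrioventricular block".

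The only reason offered is a short reference to clinical considerations. By contrast, the same section gives an actual argument for restricting cost and length of stay to the postoperative period.

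The data for the listed endpoints are still gathered. Protocol section 6.4 collects "Transthoracic echocardiography and 12-lead-ECG at the 30 day after discharge" and "Any arrhythmias experience confirmed by ECG and related treatment". Section 1.4 of both documents names arrhythmia as a hazard of the procedure: "Potential risks are as follows: extending operation time, increasing intraoperative blood loss and postoperative arrhythmias".

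**The concern.** The latest documents hold two event thresholds for each of two harm outcomes, and only the narrower one is analysed. Protocol amendment 1 changed the exclusion criteria and nothing else, so the protocol still promises the unrestricted outcomes. The SAP's own endpoint list does too. The SAP has no general adverse-event analysis that would pick up what section 8.1 leaves out.

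Two things are at stake. First, an effusion below moderate size, or a rhythm disturbance found on the 30-day ECG and managed electively, enters no comparison between the arms, in a trial of a procedure for which arrhythmia is a named risk. Second, the restricted arrhythmia endpoint is defined by whether intervention was needed at once, not by the rhythm. Surgeons know the allocation, and blinded reading is specified only for the decision on POAF (section 2.1). The plan does not say who decides, for this endpoint, that a rhythm qualifies.

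**Working it through.** **The passages side by side**

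| Outcome, within 30 days after discharge | Protocol 2.2.1 and SAP 2.2.1 | SAP 8.1 | Listed version compared? |
|---|---|---|---|
| Effusion | any | new-onset and at least moderate | no |
| Arrhythmia other than AF | any | only if intervention is needed at once | no |

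Protocol Figure 1 labels the first item as delayed effusion, so the idea of delay is not new in SAP 8.1. The grade is.

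**Inputs for the size of the effect**

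- 215 per arm (SAP 3.5: 408/0.95 = 429.5, rounded up to 430). The 408 belongs to the primary endpoint. Whether it follows from its own inputs is a separate question that does not bear on this point.
- Two-sided 0.05 (SAP 8.1).
- Chi-squared or Fisher's exact test (SAP 4.2, which does not say when each applies, so both are shown).
- Event rates: none in the documents. All rates below are assumptions. There is no stated power for these endpoints to reproduce.

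**Power.** Enumerate both binomials and add up the probability of every outcome that is significant in the direction of harm:

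power = Σ Bin(a; 215, p0) × Bin(b; 215, p1), over all a < b with p-value < 0.05.

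*Scenario A: denervation doubles the event rate (p1 = 2 × p0).*

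| Control rate | Expected events, control vs denervation | Chi-squared | Fisher |
|---|---|---|---|
| 1% | 2.15 vs 4.3 | 12% | 5% |
| 2% | 4.3 vs 8.6 | 23% | 14% |
| 3% | 6.45 vs 12.9 | 32% | 25% |
| 5% | 10.75 vs 21.5 | 50% | 44% |
| 10% | 21.5 vs 43 | 84% | 80% |
| 20% | 43 vs 86 | 99.6% | above 99% |

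*Scenario B: denervation adds a fixed 5 percentage points.*

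| Background rate | Chi-squared | Fisher |
|---|---|---|
| 1% | 86% | 77% |
| 20% | 24% | 20% |
| 30% | 20% | 17% |

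The ranking reverses. Under A the common endpoint is much more sensitive. Under B the rare one is, because background events dilute the excess.

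**Precision.** The 95% CI of the risk ratio is RR divided and multiplied by exp(1.96 × √[(1−p0)/(215 p0) + (1−p1)/(215 p1)]).

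- 3% vs 6%: factor 2.52, so 2.0/2.52 = 0.79 to 2.0 × 2.52 = 5.04.
- 20% vs 40%: factor 1.37, so 2.0/1.37 = 1.46 to 2.0 × 1.37 = 2.74.

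**What the narrow endpoint can still show.** With no control events, 6 events in the denervation arm are significant (Fisher p = 0.030) and 5 are not (p = 0.061). A rise from 5% to 15% has 93% power (Fisher). With 80% power (normal approximation), the smallest detectable denervation rate is 5.9% from a 1% control rate and 7.8% from 2%.

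**The case against.** The substitution is declared openly in SAP 8.1 and again in the summary of changes, and a change between versions is no fault in itself. Restricting safety outcomes to clinically important events is a common and defensible choice. Scenario B shows that it can be the better one: minor background events can bury a serious excess. All of this stands, and it is why the severe-only versions should stay.

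The broad versions also have weaknesses. Follow-up may be by telephone, so mild effusion and silent arrhythmia may be missed in some patients, and SAP 8.2 does not impute. An endpoint of any arrhythmia has no lower bound; the plan does not say whether isolated premature beats would count. Power at a full 215 per arm is thus a best case for the broad versions.

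Some stronger readings are tempting, and the documents do not support them:

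- *The restricted endpoints cannot show excess harm.* They can, if the excess is large (6 vs 0 events, or 5% vs 15%).
- *The severe events are rare.* Severe events are a subset of all events, but no rate is given for either version.
- *Rhythm safety is untested short of an emergency.* SAP 6.1 compares AF episodes, AF burden, heart rates and premature atrial contractions between arms, and the primary outcome counts any supraventricular arrhythmia over 30 seconds up to day 6.
- *The thresholds were raised after outcome data were seen.* The documents say nothing either way.

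None of this supplies the missing comparison of the listed endpoints or reconciles the sections.

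**Conclusion.** The point holds as a gap in the planned safety analysis and as an unreconciled definition. Two of the five listed safety outcomes are analysed only in a severe form. Effusion below moderate size and non-critical, non-AF arrhythmia after discharge have no planned between-arm comparison, although the plan collects the data.

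The size depends on assumed rates. At a control rate of about 3% or less for the severe events, power to show a doubling is at most about 25% (Fisher) to 32% (chi-squared), so a finding of no difference would say little about a doubling. If the severe events are more frequent, or the true excess is a large absolute one, the limitation is much smaller. Neither version dominates the other, so the defect is that one replaces the other, not that a severe-only analysis exists. The primary result is unaffected. The change should be made, but the trial does not stand or fall by it.

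**What to change.** 1. In SAP 8.1, report both endpoints as listed in section 2.2.1 (any effusion; any ECG-confirmed arrhythmia other than AF) alongside the severe-only versions, each with risk difference and 95% CI.
2. Tabulate the arrhythmias by rhythm type, with the categories named in advance. The count then does not depend on the treatment decision, and trivial findings stay visible as such.
3. State, by arm, how many patients had a 30-day ECG and how many a 30-day echocardiogram, and use these as denominators, since some follow-up may be by telephone only.
4. Reconcile protocol 2.2.1, SAP 2.2.1 and SAP 8.1, and give the reason for the severity thresholds.

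The cost is SAP and protocol wording and a few rows in the safety table; no new assessments are needed. The downside is that minor events appear next to serious ones and that mild events may be incompletely ascertained, which the denominators would make plain.
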